**METHOD**

**Data source, study design, and study population**

This cohort study will be based on the nationwide histopathology cohort, Epidemiology Strengthened by histoPathology Reports in Sweden (ESPRESSO)^1^, and several healthcare registers in Sweden. ESPRESSO^1^ contains data on GI-related biopsies from all 28 pathology departments in Sweden from 1965 to 2017. The Total Population Register^2^ contains details on birth, death, and migration, which was initiated in 1968. The Prescribed Drug Register^3^ collects information on medications dispensed at all pharmacies in Sweden since July 2005, including for example dispensing date, drug name, and a defined daily dose (DDD). The National Patient Register^4^ covers data on inpatient (since 1964) and outpatient (since 2001) specialist care with disease diagnoses and surgical procedures. The Cancer Register^5^ contains data from >96% of incident cancer cases since 1958. The Cause of Death Register^6^ contains information on >99% of death since 1952. The Swedish Longitudinal Integrated Database for Health Insurance and Labour Market Studies^7^ contains information on demographic and socioeconomic characteristics (e.g., education and county of residence).

The IBD patients will be identified as those with ≥ 1 biopsy indicating IBD in the ESPRESSO and ≥ 1 International Classification of Disease (ICD) code for IBD in the NPR (see **Table 1** for the definition of IBD subtypes)^8^. Such diagnostic approach yields a positive predictive value of 95%^9^.

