**Two-step matching process**

A two-step matching process will be applied to establish the cohort. In the direct matching step, statin users and non-statin users will be matched on age at IBD diagnosis (<18, 18-<40, 40-<60, and ≥60), sex, IBD subtype (CD or UC), and calendar year at IBD diagnosis (1969-1989, 1990-1999, 2000-2009, 2010-2018). IBD-unclassified will not be considered in this project due to diagnostic uncertainty. To ensure similar opportunities for care and treatment^10^, non-statin users should have a random drug prescription (except IBD medications, see **Table 2** for ATC codes) within three months before or after the start date of statin treatment in the matched statin users. All identified non-statin users will be assigned the same index date as the index statin user. We will exclude individuals who had a record of migration, received a colectomy, or had a diagnosis of any of the following diseases before the index date: cancers, human immunodeficiency virus/ acquired immunodeficiency syndrome, primary immunodeficiency disease, end-stage renal disease, severe liver failure, and any organ transplantation (see **Table 2** for procedure and ICD codes).

In the propensity score matching step, statin users and non-statin users will be matched in a 1:1 ratio by using a greedy nearest-neighbor matching algorithm without replacement, with a caliper of 0.2 standard deviation of the logit of the propensity score^11^. A logistic regression model will be used to calculate the propensity score after adjusting for the below demographic and socioeconomic characteristics, comorbidities, and co-medications identified up to and including the index date.

- Age at IBD diagnosis, years (continuous);
- Duration of IBD, years (continuous);
- Number of healthcare visits (continuous);
- Country of birth (Nordic countries or others);
- Education (0-9, 10-12, ≥13 years, or missing);
- Comorbidities (yes/no, see Table 2 for detail): gastrointestinal diseases, intestinal infections, cardiovascular diseases, obesity/dyslipidemia, type 1 and type 2 diabetes, autoimmune diseases, obstructive sleep apnea, chronic obstructive pulmonary disease, and myositis;
- Medications (yes/no, see Table 2 for detail): antibiotics, proton pump inhibitor, antiviral medications, IBD medications, non-aspirin anti-platelet medications, aspirin, non-statin lipid lowering medications, anti-diabetic medications, anticoagulation medications, and anti-arrhythmias medications.

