**Subgroup analyses and sensitivity analyses**

We will assess whether the associations vary by the following factors: age at the index date (<60 or ≥60 years), sex, calendar period for IBD diagnosis (1969-1999 or 2000-2018), educational attainment (0-9, 10-12, ≥13 years, or “missing”), IBD subtype (CD or UC), age at IBD diagnosis (<50 or ≥50 years), duration of IBD (<10 or ≥10 years), type of statins initially treated, and type of CRC (colon cancer or rectal cancer).

Several sensitivity analyses will be conducted. First, we will construct a model in which covariates will adjusted as time-varying variables. Second, we will exclude individuals with a history of CVD before statin initiation. Third, we will discard the first year and then first two years of follow-up from the analysis. Fourth, we will evaluate the potential influence from unmeasured confounding by calculating E-values^14^. Finally, we will perform a negative control analysis using fracture as a negative control outcome to assess potential biases in our study^15^.

Data analyses will be performed using SAS version 9.4, Stata (version 16.1), and R version 3.6.0.

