| Rosuvastatin | C10AA07 |
| **Outcomes** | **ICD code** ^a^ |
| Incident colorectal cancer (CRC) ^b^ | ICD-7: 153-154, but not 1541 (anal cancer) or 1534 (appendiceal cancer) |
| CRC-related mortality | ICD-10: C18-20, but not C181 (appendiceal cancer) |
| All-cause mortality | ICD-10: A00-U99 |
| **Proctocolectomy and colectomy** | **Procedure code** |
| Proctocolectomy ^c^ |  |
|  | Sixth version (1969-1996): 4652, 4653, 4654 |
|  | Seventh version (1997-): JFH20-JFH40 |
| Colectomy with an intact rectum ^d^ |  |
|  | Sixth version (1969-1996): 4650, 4651 |
|  | Seventh version (1997-): JFH00, JFH01, JFH10, JFH11, JFH96 |
| Rectum amputation after a colectomy with an intact rectum ^e^ |  |
|  | Sixth version (1969-1996): 4820, 4821, 4822, 4828 |
|  | Seventh version (1997-): JGB00-JGB97 |
| **Exclusion criteria** | **ICD-10 code/procedure code** |
| Cancer | C00-C97, except non-melanoma skin cancer (C44) |
| HIV/AIDS | B20-B24, F024, O987, R75, Z114, Z219, Z711 |
| Primary immunodeficiency disease | D71, D80–D84 |
| Severe liver failure | B150, B160, B162, B190, K704, K72, K766, I85 |
| End-stage renal disease | N18.5,  N18.6, Z49, Z99.2, Z94.0; Procedure codes: 9200; V9200; 9212; V9212; 9314; V9531; DR012; DR013; DR016; DR024; QF006; 9211; V9211; 9213; V9213; V9532; DR015; DR023; DR055; DV056; 9219; V9219; 9223; V9223; DR017; DR020; DR055; DR056; 6070; KAS10; KAS20 |
| Any organ transplantation | Swedish surgery codes (KVÅ codes): KAS, FQA, FQB, GDG, JJC |
| **Comorbidities** | **ICD-10 code** |
| Gastrointestinal diseases | K00-K99 |
| Intestinal infections | A00-A09 |
| Cardiovascular diseases | I00-I99 |
| Obesity/dyslipidemia | E78 , E65, E66 |
| Type 1 and type 2 diabetes | E10-E14 , O24 |
| Autoimmune diseases | E035, E039, E050, E055, E059, E063, E065, G35, M05-M09, M32, L40 |
| Obstructive sleep apnea | G473 |
| Chronic obstructive pulmonary disease (only if diagnosed ≥40 years) | J41-J44 |
| Myositis (no adequate codes present for rhabdomyolysis) | M60 |
| **Medications** | **ATC code** |
| Antibiotics | J01 |
| Proton pump inhibitor | A02BC |
| Antiviral drugs | J05 |
| IBD medications |  |
| Immunomodulators |  |
| Azathioprine | L04AX01 |
| Mercaptopurine | L01BB02 |
| Methotrexate | L04AX03/L01BA01 |
| Anti-TNF treatment |  |
| Infliximab | L04AB02 (L04AA12 before 2008) |
| Adalimumab | L04AB04 (L04AA17 before 2008) |
| Golimumab | L04AB06 |
| Vedolizumab | L04AA33 |
| Systemic corticosteroids |  |
| Betamethasone | H02AB01 |

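### The propensity score contains no pre-index bowel biopsy or endoscopy history and no dysplasia or adenoma status, and no planned balance check or sensitivity analysis targets this gap

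*SAP*

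**What the plan says.** In the SAP, Two-step matching process, the direct step matches on age at IBD diagnosis, sex, IBD subtype and calendar period of diagnosis. For the second step, "A logistic regression model will be used to calculate the propensity score after adjusting for the below demographic and socioeconomic characteristics, comorbidities, and co-medications". The list comprises age at IBD diagnosis, IBD duration, visits, country of birth, education, nine comorbidity groups and ten medication groups.

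The entries closest to bowel care and bowel pathology are:

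- "Number of healthcare visits (continuous"), with no restriction to gastroenterology or endoscopy;
- in Table 2, "Gastrointestinal diseases | K00-K99", as one yes/no flag.

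Non-users must also have a non-IBD prescription within three months of the matched user's start. The stated purpose is "To ensure similar opportunities for care and treatment". The cancer exclusion in Table 2 is "C00-C97, except non-melanoma skin cancer (C44"). Prior colectomy is excluded as well.

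Under Data source, study design, and study population, ESPRESSO "contains data on GI-related biopsies from all 28 pathology departments in Sweden from 1965 to 2017", and "IBD patients will be identified as those with ≥ 1 biopsy indicating IBD in the ESPRESSO". Footnote b of Table 1 shows that topography codes T67 and T68 mark the colon.

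Under Subgroup analyses and sensitivity analyses, the safeguards include time-varying covariates, one- and two-year lags, E-values and a fracture outcome: "we will perform a negative control analysis using fracture as a negative control outcome to assess potential biases in our study".

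**The concern.** The hypothesis is that statin users have a lower risk of CRC. How closely a patient's bowel has been examined, and whether premalignant lesions were already present, plausibly affect later CRC. Either could also differ between people who start a preventive drug and people who do not. If so, the matched comparison carries confounding that the plan does not measure.

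The listed covariates can all be balanced while bowel investigation is not. Statin starters plausibly have more cardiovascular or diabetes visits, so equal visit totals can hide unequal bowel follow-up. The balance check covers the covariates, so it would not reveal an imbalance in a variable that was never derived. Yet the cohort is built from biopsy records, so a biopsy-based measure is within reach.

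**Working it through.** **1. Does any listed item capture the missing information?**

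| Item in the SAP | What it captures | Gap |
|---|---|---|
| Direct matching factors | Age at diagnosis, sex, subtype, period | No bowel investigation history |
| Visit count | All contacts | Not bowel-specific |
| K00-K99 flag | Any digestive diagnosis | Contains K50 and K51, which Table 1 uses to define CD and UC |
| Prescription requirement | Contact with care | Not bowel-specific |
| C00-C97 exclusion | Prior cancer | No code listed for dysplasia or adenoma |
| Medication flags | Treatment, including IBD drugs | Disease activity at most |

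The K00-K99 flag is nearly, not exactly, constant. It could be negative for a patient whose IBD was coded only before ICD-10 and who has had no K code since. Such a patient is not the contrast of interest.

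**2. Does any planned analysis target it?** The standardized differences do not cover it. The time-varying model names no new covariate. The lags address only the first one or two years. E-values state how strong a confounder would have to be but do not remove it. Fracture does not depend on bowel examination, so it is at best an indirect check.

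**3. How large could it be?** The SAP gives no sample size, event count or expected hazard ratio, so there is no figure to reproduce. The inputs below are assumptions chosen to show scale. For one binary confounder with prevalence p1 in users and p0 in non-users, and relative risk RR for CRC, the ratio seen under a true null is

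[1 + p1(RR − 1)] / [1 + p0(RR − 1)].

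| Confounder | p1 | p0 | RR | Arithmetic | Null ratio |
|---|---|---|---|---|---|
| Recent bowel investigation | 0.45 | 0.40 | 0.6 | 0.82/0.84 | 0.976 |
| same | 0.45 | 0.40 | 0.4 | 0.73/0.76 | 0.961 |
| same | 0.50 | 0.40 | 0.6 | 0.80/0.84 | 0.952 |
| same | 0.60 | 0.40 | 0.4 | 0.64/0.76 | 0.842 |
| Prior dysplasia | 0.02 | 0.03 | 5 | 1.08/1.12 | 0.964 |
| same | 0.02 | 0.04 | 8 | 1.14/1.28 | 0.891 |

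The range is 0.84 to 0.98. Harsher inputs go lower: dysplasia in 5% against 10% with RR 10 gives 1.45/1.90 = 0.763. Swapping the two groups in the fourth row gives 0.76/0.64 = 1.19, so the bias can also mask a benefit.

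**4. How do these imbalances compare with the plan's 10% limit?** The standardized difference for a binary variable is |p1 − p0| / √{[p1(1 − p1) + p0(1 − p0)]/2}.

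- 45% v 40%: 0.05/0.494 = 0.10, at the limit.
- 50% v 40%: 0.10/0.495 = 0.20.
- 60% v 40%: 0.20/0.490 = 0.41.
- 2% v 3%: 0.01/0.156 = 0.06, which would pass as balanced.
- 2% v 4%: 0.02/0.170 = 0.12.

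**5. What would E-values say?** With E = 1/HR + √[(1/HR)(1/HR − 1)], assumed hazard ratios of 0.6, 0.7, 0.8 and 0.9 give 2.72, 2.21, 1.81 and 1.46. A modest association is within reach of an omitted confounder. A strong one needs a large imbalance or a very strong risk factor.

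**The case against.** Covariate choice is a matter of judgement, and nothing in the SAP is contradicted by the omission. The plan has several partial safeguards: the prescription requirement, the visit count, the colectomy exclusion, the lags, the E-values, and a cancer-stage analysis (labelled non-prespecified) that bears on earlier detection. The larger surveillance biases above need standardized differences two to four times the plan's limit, persisting after matching on visits, IBD duration, IBD medications, education and calendar period. At an imbalance close to the limit the bias is only 2% to 4%. All of this stands, and it keeps the point modest.

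A reader might also infer four stronger claims that the document does not support.

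- **That dysplasia and surveillance are both already measured.** The SAP establishes GI biopsies up to 2017. Table 1 lists only codes for IBD and inflammation. Nothing says that dysplasia or adenoma is coded or was extracted, or that a biopsy's indication is known.
- **That a lower CRC risk could not be separated from closer surveillance.** E-values and lags allow some separation, and a strong association would be hard to explain this way.
- **That the fracture control is uninformative here.** If a general health-seeking tendency drives both statin use and bowel follow-up, fracture may pick up part of it. It would miss an imbalance specific to the bowel.
- **That the bias must favour statins.** Removal of precursors lowers incidence, but earlier detection brings diagnoses forward and does not lower incidence. The document does not show which group is examined more.

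The SAP is at its third version, after external review. Re-running the primary match now could itself be a post-hoc change, and the fix allows for that.

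**Conclusion.** The point holds as a gap in confounding control for the primary outcome. The propensity score has no measure of pre-index bowel biopsy or endoscopy history and no dysplasia or adenoma status. Its nearest proxies are poor, and no planned analysis targets the gap.

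Direction is not fixed. Size is unknown: the null ratios of about 0.84 to 0.98 illustrate bias towards benefit and rest wholly on assumed prevalences and relative risks. They show that a modest association could be partly or wholly explained, not that one would be. This is a worthwhile, inexpensive improvement. It does not show that the planned analysis is invalid.

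**What to change.** 1. From ESPRESSO, derive the number of distinct dates with a T67 or T68 biopsy in a fixed window before index, for example three to five years, and state the window in the SAP.
2. Add this count to the propensity model. If the primary match is already fixed, use it in a sensitivity re-match labelled as non-prespecified, as the SAP does for its other late additions.
3. Report its standardized mean difference, with the distribution by group.
4. If dysplasia or adenoma is coded in the extracted data, add prior dysplasia/adenoma (yes/no) and a sensitivity analysis excluding those patients. Report counts as well as the standardized difference, since a rare but strong risk factor can pass the 10% limit. If it is not coded, say so as a limitation.
5. Replace the K00-K99 flag with specific conditions, or at least exclude K50 and K51 from it.

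The cost is a few derived variables and one further match. There are three drawbacks. Slightly fewer pairs may fall within the caliper. The count will reflect flares as well as surveillance, so it is a proxy. Biopsy data end in 2017, so for an index date at the end of 2019 about two years of a three-year window are unobserved; an analysis restricted to index dates up to 2017 would show whether this matters.

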**Identification of statin users**

Statin use will be identified from the Prescribed Drug Register by the Anatomical Therapeutic Chemical (ATC) code C10AA, including lipophilic statins (simvastatin and atorvastatin) and hydrophilic statins (pravastatin and rosuvastatin) (see **Table 2** for ATC codes). Statin users will be identified as those aged ≥ 18 years and with a statin prescription for ≥30 cumulative DDD (cDDD) from July, 2006 or later. The date that an individual first attained a cDDD ≥ 30 for a statin will be defined as the index date for statin exposure. Individuals who had any statin prescription before July 2006, before IBD diagnosis or before the first attainment of cDDD ≥ 30 will be excluded from the analysis to ensure a new-user design. We will use the intention-to-treat analysis as the main analysis.

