**Identification of primary and secondary outcomes**

Follow-up will begin at index date until the first recorded date of incident CRC, proctocolectomy, emigration, death, or end of follow-up (Dec, 2019). A patient who had a colectomy but had an intact rectum will be considered at risk of rectal cancer until proctectomy (see **Table 2** for procedure codes). The primary outcome is incident CRC (see **Table 2** for ICD codes), while secondary outcomes are CRC-related mortality and all-cause mortality (see **Table 2** for ICD codes).

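### Propensity-score drug flags and the visit count have no fixed look-back, so they cannot separate current from long-past use and the 10% balance check cannot see the difference

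*SAP*

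**What the plan says.** Under Two-step matching process, one logistic model gives the propensity score from demographic factors, "comorbidities, and co-medications identified up to and including the index date". The drug classes are listed as "Medications (yes/no, see Table 2 for detail") and care contact as "Number of healthcare visits (continuous"). Table 2 supplies codes for the drug classes but no time windows, and the visit count has neither a window nor a per-year scale. Calendar year of the index date is not among the listed covariates.

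The data limits are given elsewhere. The drug register "collects information on medications dispensed at all pharmacies in Sweden since July 2005", and the patient register "covers data on inpatient (since 1964) and outpatient (since 2001) specialist care" (both under Data source, study design, and study population). Statin users are those "with a statin prescription for ≥30 cumulative DDD (cDDD) from July, 2006 or later" (Identification of statin users). Follow-up stops at "end of follow-up (Dec, 2019") (Identification of primary and secondary outcomes). Non-users take the index date of their matched user and must have some non-IBD prescription within three months either side of that user's statin start. The paragraph after the covariate list treats a covariate as balanced when its standardized mean difference is below 10%.

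**The concern.** With an end point but no start point, a drug flag as written means any dispensing since the register opened. The same yes therefore describes the past year for someone entering in July 2006 and up to 14.5 years for someone entering at the end of 2019. A single coefficient per drug class is fitted across all of them.

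Part of what the score has to capture is drug use and care contact around the time a statin is started. A flag that puts a person now taking a drug together with someone dispensed it once a decade ago measures this poorly, and so does a visit total with no time scale. The balance check inherits the weakness, because it looks only at the covariates as defined. A table with every difference below 10% could then be read as showing comparability in recent use and contact, which it would not have tested. This concerns the main confounding control for the primary outcome.

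**Working it through.** The SAP states no look-back length, so there is no figure of its own to reproduce.

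**Step 1: look-back.** Look-back = index date minus register start. The inputs from the SAP are drug data from 2005.5, outpatient data from 2001.0 and earliest index 2006.5. No last index date is given, so the end of follow-up (2020.0) serves as an upper bound.

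| Index date | Drug look-back (years) | Outpatient look-back (years), if all register time is counted |
| --- | --- | --- |
| July 2006 | 2006.5 − 2005.5 = 1.0 | 2006.5 − 2001.0 = 5.5 |
| January 2010 | 4.5 | 9.0 |
| January 2015 | 9.5 | 14.0 |
| End of 2019 | 2020.0 − 2005.5 = 14.5 | 2020.0 − 2001.0 = 19.0 |

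**Step 2: how much of an ever-flag is current use.** Assumption: a share p = 20% has a dispensing of the drug class in any one year. With a constant rate the flagged share after L years is E = 1 − (1 − p)^L. With use clustered in some people (gamma-distributed rates, shape k), E = 1 − (1 + mL/k)^(−k), where m = k[(1 − p)^(−1/k) − 1]. The share of flagged people with use in the last 12 months is q0 = p/E.

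- Constant rate: E = 20%, 63%, 88% and 96% at 1, 4.5, 9.5 and 14.5 years, so q0 = 100%, 32%, 23% and 21%.
- Strong clustering (k = 0.2): E = 20%, 37%, 45% and 50%, so q0 = 100%, 54%, 44% and 40%.

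**Step 3: what the balance check misses.** Assumptions: the ever-flag is exactly balanced between arms, look-back is the same in both arms, and recent use multiplies the odds of statin start by OR = 1.5 or 2. Among flagged users the recent share q1 has odds OR × q0/(1 − q0). The share with 12-month use is then E × q1 in users and p in non-users. The standardized mean difference (SMD) is (E·q1 − p) / √{[E·q1(1 − E·q1) + p(1 − p)]/2}.

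Worked case (constant rate, L = 14.5, OR = 2):
- q0 = 0.200/0.961 = 0.208, with odds 0.263. Doubled, this gives q1 = 0.345.
- Recent use in users = 0.961 × 0.345 = 0.331.
- SMD = (0.331 − 0.200) / √[(0.331 × 0.669 + 0.200 × 0.800)/2] = 0.131/0.437 = 0.30.

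| Drug look-back (years) | Constant rate, OR 1.5 / 2 | Strong clustering, OR 1.5 / 2 |
| --- | --- | --- |
| 1.0 | 0.00 / 0.00 | 0.00 / 0.00 |
| 4.5 | 0.14 / 0.24 | 0.09 / 0.14 |
| 9.5 | 0.16 / 0.29 | 0.11 / 0.18 |
| 14.5 | 0.17 / 0.30 | 0.12 / 0.20 |

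With p = 10% the values at 4.5 to 14.5 years run from 0.08 to 0.23. These figures treat one drug class on its own. Other terms in the score that correlate with recent use would reduce them by an amount the SAP does not allow one to compute.

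**The case against.** The best defence is that users and their directly matched non-users share an index date, so within a set neither arm has more history recorded than the other. That is right, and it rules out reading the plan as capturing drugs unequally by arm. Such inequality would need propensity matching to cross index-date sets, which the SAP neither states nor excludes. Step 3 already assumes equal look-back, and the imbalance remains.

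Second, the three-month prescription requirement ties non-users to recent contact. It does ensure some contact. But any one non-IBD drug qualifies, even after the index date, so neither specific drug use nor visit intensity is balanced by it.

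Third, using all available history is a respectable choice, above all for chronic disease and long-term drugs. That stands, and is why the ever-flags should stay. Age at IBD diagnosis and IBD duration are also both in the score and add up to age at index, so a visit total's dependence on age is partly absorbed.

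Fourth, the time-varying covariate model, the E-values and the fracture negative control probe residual confounding. None of them sets a baseline window or changes the matched cohort.

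Three stronger readings are tempting but unsupported:
- **Flags saturate near 100%.** This needs unclustered use of a common drug. With clustering, 50% to 78% are flagged at 14.5 years for p = 20% (k = 0.2 to 1).
- **The covariates no longer measure use at statin start.** Current users are always flagged; they are merely mixed with past users.
- **Register coverage alone could produce a difference in the subgroup comparison by "calendar period for IBD diagnosis (1969-1999 or 2000-2018").** Look-back runs from register start to index, whatever the diagnosis date. With diagnosis and index dates assumed uniform, mean drug look-back is 7.8 years for the earlier group and 8.9 for the later. At 0.2 fills per year, 72% and 77% are flagged.

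**Conclusion.** The point holds as a loss of resolution in the propensity score and in its balance check. As written, drug look-back runs from 1.0 to at most 14.5 years. For visits the defect is that no window is stated. That they are a lifetime total is an inference, and if so the outpatient range is 5.5 to 19 years, not the drug range.

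On the assumptions shown, a perfectly balanced ever-flag leaves an SMD of about 0.1 to 0.3 in 12-month use at look-backs of 4.5 years or more. Most of these values exceed the plan's own limit; the weakest scenarios fall just under it. The result rests on an assumed annual use and an assumed link between recent use and statin start, neither of which the SAP gives. It does not show which way, or how far, the hazard ratio would move. This is a worthwhile, inexpensive improvement, not an error that invalidates the design.

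**What to change.** In the list of propensity-score covariates and in the balance table, add for each drug class an indicator of any dispensing in the fixed 12 months before the index date. Add visit counts over the same 12 months, inpatient and outpatient separately. Every entrant has this window, because the earliest index date falls one year after drug data begin and outpatient data begin in 2001. Keep the ever-flags for comorbidities and drugs, since replacing all history by 12 months would trade missed history for recency. Apply the 10% rule to the 12-month versions as well.

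The cost is SAP wording and re-derivation of covariates from data already held. The downside is more terms in the score and possibly a few more unmatched statin users.

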**HYPOTHESIS**

Statin use is associated with lower risk of the development of CRC, CRC-related mortality, and all-cause mortality in patients with IBD.

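### The propensity score covers several serious diseases but omits dementia, non-end-stage kidney disease and any frailty or comorbidity index, so the secondary all-cause mortality HR may be biased toward benefit.

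*SAP*

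**What the plan says.** The SAP's Hypothesis section states that "Statin use is associated with lower risk of the development of CRC, CRC-related mortality, and all-cause mortality in patients with IBD". All-cause mortality is a secondary outcome; incident CRC is primary. The comparator is non-users of statins, not starters of another drug.

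Under Two-step matching process, the propensity score contains:

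- age at IBD diagnosis, IBD duration, country of birth and education;
- one general utilisation measure, "Number of healthcare visits (continuous", with no look-back window or visit type given;
- nine yes/no comorbidity flags: "gastrointestinal diseases, intestinal infections, cardiovascular diseases, obesity/dyslipidemia, type 1 and type 2 diabetes", then "autoimmune diseases, obstructive sleep apnea, chronic obstructive pulmonary disease, and myositis";
- ten medication groups, among them anti-platelet, anticoagulant, anti-arrhythmic and anti-diabetic drugs.

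The same section excludes patients with earlier "cancers, human immunodeficiency virus/ acquired immunodeficiency syndrome, primary immunodeficiency disease, end-stage renal disease, severe liver failure, and any organ transplantation".

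Table 2 defines the flags broadly. Circulatory disease is the whole chapter ("Cardiovascular diseases | I00-I99"), and the lung flag is "Chronic obstructive pulmonary disease (only if diagnosed ≥40 years) | J41-J44". The gastrointestinal flag is K00–K99.

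Under Subgroup analyses and sensitivity analyses, the plan adds one- and two-year lags, E-values, and a "negative control analysis using fracture as a negative control outcome to assess potential biases in our study".

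**The concern.** A score built on the indications for statins pairs each user with someone who had a similar predicted chance of treatment but did not start. Frailty or limited life expectancy is a plausible reason for not starting a preventive drug. That is an assumption; the SAP does not discuss it. If it holds and the reason is not in the score, matched non-users carry more of it and die sooner for reasons unrelated to statins. The mortality HR then moves in the hypothesised direction.

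Three features of the list matter here.

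- No item covers dementia, kidney disease at stages N18.1–N18.4 (the exclusion starts at N18.5), alcohol-related disease as such, severe psychiatric disease, inpatient days, number of drugs, or an overall frailty or comorbidity index.
- Chronic liver disease falls nominally within K00–K99, but so do K50 and K51, the ICD-10 codes that define the cohort in Table 1. No carve-out is stated. Nearly every patient with IBD coded since 1997 would score yes, so the flag can hardly balance liver disease.
- The single circulatory flag scores hypertension and advanced heart failure alike.

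At stake is whether a lower mortality HR could be credited to statins. The SAP does not say which outcomes its 10-year NNT covers; an NNT computed for mortality would inherit the same bias.

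**Working it through.** The SAP gives no expected mortality HR, event count or frailty prevalence, so there is no plan figure to reproduce. All prevalences, ratios and death rates below are assumptions.

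**Apparent HR when the true HR is 1.** For one binary unmeasured factor with residual prevalence p1 in users and p0 in non-users after matching, and mortality ratio R:

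HR = [1 + p1(R − 1)] / [1 + p0(R − 1)]

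| p1 (users) | p0 (non-users) | R = 2 | R = 4 |
| --- | --- | --- | --- |
| 3% | 5% | 1.03/1.05 = 0.981 | 1.09/1.15 = 0.948 |
| 3% | 6% | 1.03/1.06 = 0.972 | 1.09/1.18 = 0.924 |
| 3% | 8% | 1.03/1.08 = 0.954 | 1.09/1.24 = 0.879 |
| 4% | 5% | 1.04/1.05 = 0.990 | 1.12/1.15 = 0.974 |
| 4% | 6% | 1.04/1.06 = 0.981 | 1.12/1.18 = 0.949 |
| 4% | 8% | 1.04/1.08 = 0.963 | 1.12/1.24 = 0.903 |

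The span is 0.99 to 0.88. With equal prevalence it is 1.00. A wider assumed gap (5% vs 15%, R = 4) gives 1.15/1.45 = 0.79.

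**Would the balance check see it?** The SAP accepts a standardized mean difference below 10%. For 3% vs 6% the difference is 0.03/√[(0.03×0.97 + 0.06×0.94)/2] = 0.145, above that limit. It would go unseen because the factor is not in the table. At the mild end (4% vs 5%) it is 0.048 and would pass even if measured.

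**Does the lag remove it?** Take 3% vs 6%, R = 4 and an assumed baseline death rate of 2% per year. After two years the frail fraction shrinks by the factor e^(−3×0.02×2) = 0.887 relative to the rest, leaving 2.67% vs 5.36%. The HR among survivors is (1 + 3×0.0267)/(1 + 3×0.0536) = 0.931, against 0.924 at the start. By year 10 it is 0.953. The two-year lag therefore removes little.

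**Spurious NNT for death at 10 years.** Holding HR at 1.09/1.18 throughout, NNT = 1/[(1 − F)^HR − (1 − F)], with F the non-users' 10-year mortality. For F = 10%, 20% and 30% the NNT is about 138, 73 and 52. Allowing the frail to be depleted at the 2% baseline rate (F about 20%), the risk difference is 0.03 × (e^(−0.2) − e^(−0.8)) = 0.0111, so the NNT is about 90 rather than 73.

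**What partial capture would do.** If added proxies removed half of the 3-point gap (3% vs 4.5%, R = 4), the HR would be 1.09/1.135 = 0.960. Full capture gives 1.00.

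**The case against.** A reader might infer that the score has no marker of life-limiting illness apart from the visit count. The document does not support that. COPD, all circulatory disease (so heart failure and stroke), diabetes and several related drug groups are in the score. Age at IBD diagnosis plus IBD duration gives attained age. The exclusions remove cancer, HIV/AIDS, primary immunodeficiency and transplantation as well as end-stage renal disease and severe liver failure.

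A reader might also infer that the mortality HR will certainly be lowered. That too goes beyond the document. Every scenario above assumes more frailty in non-users, so the direction is an input. Two forces oppose it. Within a single yes/no circulatory flag, users may have the more severe disease. And a non-user may qualify through a prescription up to three months after the index date, which requires survival to that date and lowers early non-user mortality. The first is only partly handled by the score; the second is confined to three months.

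The planned E-values, lags and fracture control deserve credit: a non-null fracture result could reveal this bias. But they gauge it rather than reduce it, and the SAP gives no rule for what a non-null fracture result would mean for the mortality conclusion.

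It is also fair that the outcome is secondary, that no effect on the primary CRC result is shown, and that choosing covariates is a judgement rather than an internal contradiction. These points limit the weight of the concern, but the omission remains.

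**Conclusion.** The point holds as a gap in covariate choice that affects a secondary outcome. The score covers several serious comorbidities, and some of the gravest conditions are excluded. It still lacks dementia, non-end-stage kidney disease, alcohol-related and severe psychiatric disease, inpatient days, drug count and any summary index, and its gastrointestinal flag cannot do the work of a liver flag. With a non-user comparator, the all-cause mortality HR may be biased toward benefit.

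The size cannot be determined from the document. Under the stated assumptions the spurious HR lies between 0.99 and 0.88, with 0.92 for the middle example. It rests on residual imbalance after matching on everything already listed. If the existing covariates absorb most of the frailty difference, the bias is negligible.

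**What to change.** Add to the propensity score and the balance table, from the Patient and Prescribed Drug Registers:

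- dementia (diagnoses F00–F03 and G30; dispensings N06D);
- chronic kidney disease N18.1–N18.4;
- chronic liver disease as its own flag, separate from K50/K51;
- alcohol-related disease and severe psychiatric disease;
- inpatient days and number of distinct drugs in the year before index.

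One register-based comorbidity or frailty index could replace these items. A sentence stating how a non-null fracture result would limit the mortality conclusion would also help.

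The cost is SAP wording, code lists, a re-match and possibly slightly fewer matched pairs. The gain will be partial: the SAP describes the Patient Register as inpatient and outpatient specialist care, so conditions managed elsewhere will be captured incompletely.
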